## Abstract

**Background:**

The use of preventive behaviors of musculoskeletal disorders (MSDs) requires proper training, which leads to correct decisions regarding maintaining postures at work and performing stretching exercises. Due to very repetitive work, applying manual force, improper postures, and static contractions of proximal muscles, assembly-line female workers suffer from musculoskeletal pains. It is assumed that structured and theory-based educational intervention using a learning-by-doing (LBD) approach may increase the preventive behaviors against MSDs and reduce the consequences of these disorders.

**Methods:**

This randomized controlled trial (RCT) will be conducted in three phases: phase 1: validation of the compiled questionnaire, phase 2: determining the social cognitive theory (SCT) constructs that predict the preventive behaviors of MSDs in assembly-line female workers, and phase 3: designing and implementing the educational theory. The educational intervention is based on the LBD approach, and the study population includes assembly-line female workers in electronic industries of Iran, who are randomly divided into two intervention and control groups. The intervention group received the educational intervention in the workplace and the control group does not receive any intervention. The theory-based educational intervention includes evidence-based information along with pictures, fact sheets, and published literature about a good posture at work and the need to perform proper stretching exercises. The educational intervention aims to improve the knowledge, skills, self-efficacy, and intention of assembly-line female workers to adopt preventive behaviors of MSDs.

**Discussion:**

The present study will evaluate the effects of maintaining a good posture at work and performing stretching exercises on the adherence to preventive behaviors of MSDs among assembly-line female workers. The developed intervention is easily implemented and evaluated in a short period of time based on the improved score of the rapid upper limb assessment (RULA) method and the mean score of adherence to stretching exercises and can be provided by a health, safety, and environment (HSE) expert.

**Trial registration:**

ClinicalTrials.gov IRCT20220825055792N1. Registered on 23 September 2022 with the IRCTID.

## Background

Work-related musculoskeletal disorders (WMSDs) are one of the main causes of activity limitation among the working population, the second most common work-related disease, and the fourth leading cause of health-related costs worldwide [1–4]. The high prevalence of these disorders and the need to control risk factors have been mentioned in some studies in recent decades [5–8]. Carrying out repetitive movements and static and improper postures at work and applying manual force are some occupational risk factors for WMSDs among assembly-line workers [9, 10]. WMSDs have led to absenteeism from the work and increased costs and human injuries and are considered as the main cause of disability and impose a significant financial burden on the health care system, individuals, and social care systems in developed and developing countries [11–14].

Ergonomic interventions and corrective measures are standard approaches to prevent WMSDs and increase productivity in the workplace; however, certain factors such as background factors, incorrect interventions, ineffective stakeholder participation, and poor ergonomic analysis can lead to unsuccessful interventions [15]. High-quality ergonomic interventions and exercise at the workplace help to prevent or control WMSDs symptoms [16]. According to the evidence, if workplace exercises are not combined with complementary ergonomic interventions, they will not be very effective [17].

One of the appropriate methods for predicting the risk of WMSDs in various tasks is the rapid upper limb assessment (RULA) [18]. The traditional scoring system of RULA has low sensitivity to input variables, and it is difficult to show the effectiveness of ergonomic interventions in it, while a single value in RULA can belong to several sets with different degrees [19]. This method is able to predict the effectiveness of various interventions in reducing the risk of WMSDs [20]. Despite the benefit of using RULA in measuring the ergonomic behaviors, applying theory-based interventions are recommended in previous studies. As it was argued, individual and environmental factors and maintaining correct sitting postures at work are among the effective factors in preventing WMSDs [21]. Therefore, one of the related theories is social cognitive theory (SCT), which considers processes of cognitive, environmental, and behavioral patterns together and recommends strategies to increase behavioral ability, self-efficacy, and expected outcomes [22]. Training can be more effective when participants are made to practice the recommended behavior and exercises are presented to them compared to the time when a lecture on the recommended behavior is given to them [23]. The learning by doing (LBD) approach is a type of active learning that leads to greater understanding and participation of people in the learning process [24]. Previous studies have used educational theories in their intervention process even in non-industrial environments [25–28], whereas most of the studies that reported the effectiveness of intervention on workers’ performance in the workplace did not use a theory-based or structured training approach [29, 30]. Although the effectiveness of SCT in improving the preventive behaviors of WMSDs has been reported in some studies [31, 32], the effectiveness of this theory in adhering to the recommended behaviors in assembly-line workers that are exposed to many risk factors for WMSDs has not been investigated efficiently [10, 33].

In addition to the direct impact on workers’ health and work disability, sickness absence, disability pensions, loss of productivity, disruption of women’s social roles, and their functional limitation due to WMSDs have negative effects on their quality of life and impose a major socio-economic burden; thus, it is known as a challenge in the work environment [34, 35]. Since health education is one of the main factors for creating health promotion in the primary health care system [36], it is important for researchers to demonstrate the role of theory-based education with an LBD approach in female assembly workers, as it improves clinical practice and scientific research. Furthermore, HSE experts can easily implement structured and theory-based training using the LBD approach in the industry, which will be of great assistance to the health system. Therefore, investigating the theory-based educational intervention of assembly-line female workers using the LBD approach can be an appropriate intervention to encourage them to use preventive behaviors of WMSDs that should be tested. The present article explains the protocol of our study with the aim of determining the effect of SCT-based ergonomic intervention on preventive behaviors of MSDs in assembly-line female workers.

## Method

### Study design

In this protocol, a double-blind, a single-center superiority randomized control trial (RCT) (control: intervention = 50%:50%), parallel controlled with voluntary participation, and 6 months follow-up will be done.

### Study setting

The present study will be conducted in Khorasan-Razavi province, located in the northeast of Iran. Iran is a country with more than 80 million populations, which is divided into 31 provinces. The first level of country subdivisions of Iran is the provinces [37]. Eligible participants will be selected from electronic industries. The study protocol approved by the Ethics Committee of Tarbiat Modares University and registered in the Iranian Registry of Clinical Trials with the number IRCT20220825055792N1. The enrollment, interview, intervention, and evaluation schedule is shown in Table 1. This protocol was developed and reported according to the Standard Protocol Items: Recommendations for Interventional Trials (SPIRIT) [38], and the clinical trial will be conducted and reported in accordance with the consolidated standards of reporting trials (CONSORT). To achieve the objective of the study, the following three phases will be considered (Table 2).

**Table 1 Tab1:**
[figure not shown]
Schedule of enrolment, interviews, intervention, and assessment of the Ergonomic Intervention trial, following the Standard Protocol Items Recommended for Clinical Trials (SPIRIT) guidelines

**Table 2 Tab2:** The study overview

Phases and participant	Aim	Methods
Phase 1: Development and psychometric of tool assessment	Validation and reliability of the questionnaire and preparation of the final questionnaire	By the research team and expert panel through face and content validity, exploratory factor analysis, reliability, and impact score
Phase 2: Descriptive study		
Determining the most important predictive structures	Identifying the most important predictive structures of social cognitive theory in applying recommended behaviors	Based on a cross-sectional study
Phase 3: The randomized controlled trial		
Design the educational interventional	Step1: Set the educational content	Based on phase 2
Implementation of the intervention	Step2: Transfer concepts to the intervention group	Based on step 1in phase 3
Educational program evaluation	Step3: Investigating the effect of the educational program in the intervention group	Fuzzy RULA method, researcher-made questionnaire, Nordic questionnaire

### Phase 1: Development and psychometric assessments

The researcher-made questionnaire will be designed based on the SCT constructs after reviewing student theses, articles, and similar questionnaires, and then the primary instrument for analyzing the psychometric properties will be prepared.

### Phase 2: Descriptive study

To assess WMSD prevalence, the researcher-made questionnaire and the Nordic questionnaire [39] will be completed in a self-reported manner by the assembly-line female workers. Afterwards, the most important predictors of preventive behaviors of MSDs will be determined after entering data into the Bayesian network [20].

### Phase 3: The randomized controlled trial

Randomized controlled trials (RCTs) are accurate tools for investigating cause-and-effect relationships between an intervention and an outcome because randomization balances participant characteristics between groups and allows any differences in outcome to be attributed to the study intervention [40]. The flow chart of the randomized controlled protocol is shown in Fig. 1

**Fig. 1 Fig1:**
[figure not shown]
The flow chart of the randomized controlled protocol

### Eligibility criteria

In an analytical study on Iranian assembly-line female workers in 2020, the mean ± SD of the participants’ age was reported as 28.3 ± 1.81 years, and more than 60% of women reported pain in the shoulder, wrist, and back area [41]. Considering that, the present intervention will be on assembly-line female workers, and it is intended to include the majority of women in the study; therefore, the eligible age range was selected above 20 years. Assembly-line female workers, having literacy and the ability to participate in the program for at least 6 months, are among the inclusion criteria. Exclusion criteria also included being pregnant, being prohibited from doing stretching exercises by the doctor, a change in the workplace, lack of consent to continue participating, and becoming pregnant during the study. Participants will report potential adverse events that may occur during the trial.

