### Instruments

Data collection instruments will include the researcher-made questionnaire based on the SCT constructs, the Nordic questionnaire [44], and the RULA method to assess the risk of upper limb MSDs [45]. The questionnaires will be completed by the two groups before the intervention, 3, 12, and 24 weeks after the educational intervention. Table 3 shows the general characteristics of the aforementioned instruments.

**Table 3 Tab3:** Summary of the instruments used for data collection

Scale	Content	Scoring
Researcher-designed questionnaire	Structures of social cognitive theory	Totally disagree (1) to totally agree (5)
RULA	Rapid upper limb assessment	1 (no need for assessment) to 4 (immediate assessment is required) level
Nordic	Identifying musculoskeletal disorders	1 yes to no 2

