### Data analysis

Data analysis will be performed using intention-to-treat analysis in the SPSS ver. 19 software and Bayesian network model. First, exploratory factor analysis will be conducted to assess construct validity after confirming sampling adequacy based on the KMO and Bartlett’s test statistic. Second, the Bayesian network model will be used to determine the variables affecting the use of preventive behaviors for MSDs.

Third, data distribution will be investigated using the Shapiro–Wilk test. Fisher’s exact test will be used for qualitative data; independent *t*-test or Mann–Whitney test will be used to determine the mean score of the studied constructs in two control and intervention groups. Pearson and Spearman correlation tests will be used for parametric data and Kendall rank correlation for non-parametric data. Moreover, to compare the difference between the values obtained before the intervention and 3, 12, and 24 weeks after the intervention in each group, generalized mixed models of repeated measure analysis of variance will be used. Bonferroni’s correction will be used for multiple primary outcomes. The difference between the means of the independent groups will also be calculated at 95% confidence interval. *P*-value < 0.05 will be considered as the statistically significant level. No replacement of study subjects or imputation of missing data will be carried out.

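### Events that arise after enrolment are listed as exclusion criteria, and nothing keeps these women in the intention-to-treat analysis

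*Protocol article*

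**What the plan says.** In the protocol article, Eligibility criteria gives one undivided list of exclusions. It begins "Exclusion criteria also included being pregnant, being prohibited from doing stretching exercises by the doctor" and continues with "a change in the workplace, lack of consent to continue participating, and becoming pregnant during the study". There is no separate category for events during follow-up.

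Data analysis sets the principle, "Data analysis will be performed using intention-to-treat analysis", and the missing-data rule, "No replacement of study subjects or imputation of missing data will be carried out". For the comparison of arms it says that an "independent *t*-test or Mann–Whitney test will be used to determine the mean score of the studied constructs in two control and intervention groups". For change over time it says that "in each group, generalized mixed models of repeated measure analysis of variance will be used".

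On follow-up, Instruments says: "The questionnaires will be completed by the two groups before the intervention, 3, 12, and 24 weeks after the educational intervention". No section says whether a woman who meets one of the later criteria continues to be assessed, or whether she is analysed in her allocated group.

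**The concern.** Intention-to-treat means that a participant, once in the trial, is analysed in the arm she was allocated to, whatever happens next. An exclusion criterion that can be met during follow-up works the other way: it takes out women who are already in.

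Two features of this trial make that more than a matter of labels. First, adherence to stretching at work is one of the two main outcomes, and unwillingness to continue is one of the exclusions. Women who dislike or abandon the programme could therefore leave the analysis of the very outcome on which they would score badly. Second, the arms are separate industries (Sampling; Blinding). Job changes and withdrawals may differ between plants, so removal need not be balanced between the arms.

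**Working it through.** **Step 1. Which exclusions can arise after enrolment?** Enrolment is the useful boundary here, because Sampling allocates the industries first and then identifies and selects eligible workers within them.

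| Exclusion | Can apply at entry | Can arise after enrolment |
|---|---|---|
| Pregnant at entry | yes | no (a later pregnancy is listed separately) |
| Stretching medically prohibited | yes | not stated |
| Workplace change | yes | yes |
| Not consenting to continue | no | yes |
| Pregnancy beginning during the study | no | yes |

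The list names pregnancy twice, so the second mention must mean an event in follow-up. Two items are strictly post-enrolment, and a third is so when it happens during follow-up.

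**Step 2. Set the list against the analysis principle.** Excluding an enrolled woman for a row-three, row-four or row-five event, and analysing every woman as allocated, cannot both be done. No sentence in the article resolves this.

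**Step 3. Does the missing-data rule add a contradiction?** No. A likelihood-based mixed model uses every observed visit without imputing anything, so ruling out imputation is compatible with intention-to-treat.

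**Step 4. Do the named methods settle the matter?** The t-test and the Mann–Whitney test use only women with a value. The mixed model could use all observed visits, but it is worded for change within each group and its name is mixed with repeated-measures analysis of variance. The method best able to use incomplete follow-up is not tied to the between-group effect.

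**Step 5. The plan's own figure.** Sample size gives 40 per group including 10% dropout. 40 × (1 − 0.10) = 36 evaluable, and 36 / 0.90 = 40, so the inflation is consistent. The 36 cannot be reproduced, because no effect size or SD is given. Back-solving for 36 per group (two-sided 0.05, 80% power, individual level, ignoring that the industry is the unit of randomization) gives d = (1.960 + 0.842) × √(2/36) = 0.66. That value is an assumption for scale only.

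**Step 6. Illustrative loss of power**, from Φ(d√(n/2) − 1.960) with d = 0.66:

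| Removed per arm | Left of 40 | Power |
|---|---|---|
| 0% | 40 | 84% |
| 10% | 36 | 80% |
| 20% | 32 | 75% |
| 30% | 28 | 70% |

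Losses within the planned 10% cost nothing against the target.

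**Step 7. Illustrative bias.** If a fraction f of one arm is removed, and their outcome is g SD worse than that of the women retained, the arm mean shifts by f × g. Low end: 0.10 × 0.3 = 0.03 SD. High end: 0.20 × 0.8 = 0.16 SD. Neither f nor g comes from the article, and the sum assumes no matching shift in the other arm.

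**The case against.** The strongest reply is that the article never says these women's data are deleted. The list may combine entry exclusions with reasons for ending participation, with intention-to-treat governing the analysis as stated. Analysis-set definitions are often left to a full protocol or analysis plan, and the flow chart is not visible here. This is fair, and it means that a completers' analysis is not established. It does not remove the conflict: the article itself gives both the exclusions and the principle, and as worded they do not fit together.

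A second reply also stands in part: some loss is unavoidable. Withdrawn consent ends data collection under any plan, and a worker who has left the line may have no workstation posture left to score by RULA.

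A reader might also infer more than the text supports:
- **That missing data are simply dropped, against intention-to-treat.** The article rules out imputation only, and it does name a mixed model.
- **That data from weeks 3 and 12 would be lost.** Tests made at each visit would use whatever was observed at that visit. Earlier data go only if they are deleted afterwards or if a classical repeated-measures analysis is run on complete cases. Neither is stated.
- **That complete-case deletion would leave 34 to 29 of 40 per arm** (40 × 0.95³ and 40 × 0.90³). This assumes independent misses at three visits, whereas pregnancy, departure and withdrawal are more naturally lasting exits. A lasting loss of 10% leaves 36.

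**Conclusion.** The point holds as a conflict between two statements in the article. Events after enrolment are exclusion criteria, the analysis is said to be intention-to-treat, and nothing keeps the affected women in the analysis. It is worth correcting because removal could be selective on a main outcome and could differ between two plants.

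Its size is unknown. The shift of 0.03–0.16 SD rests wholly on the assumed 10–20% removed from one arm and the assumed gap of 0.3–0.8 SD. The power figures rest on an effect size back-solved from the sample size. The conclusion depends on neither. It rests on reading the exclusion list as it is worded.

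**What to change.** - **Eligibility criteria:** separate exclusions that apply at entry from events that arise after enrolment. State that all enrolled women are analysed in their allocated arm, with all data collected up to any withdrawal of consent, and that remaining assessments are sought where consent and the work setting allow. Reconcile this with the intention-to-treat statement in Data analysis.
- **Data analysis:** use the mixed model already named, fitted by likelihood to all available visits, to estimate the between-group effect (group by time), and not only change within each group. The no-imputation sentence can stay.
- **Optional:** one sensitivity analysis for missing outcomes.

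Whether a woman with one of these events goes on with the exercises is a clinical matter and is not addressed here.

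The cost is minor rewording and some follow-up contacts; the Intervention section already plans calls and messages for 12 weeks. The stated sample size does not change. Some outcomes will still be missing after withdrawal of consent or departure from the line.

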### Intervention

The intervention protocol focuses on correcting workers’ posture based on RULA by creating a fuzzy system that is helpful in most workplaces, where a large number of workers are exposed to WMSDs due to poor posture at work [42]. Exercises also include stretching and strengthening exercises of the upper limb, focusing more on the neck, hand, and wrist joints. The intervention program will be developed based on the most important predictive constructs of SCT from phase 2 of the study. The recruitment process will continue until the required sample size is reached. The researcher-made questionnaire, the standardized Nordic questionnaire, and the RULA method will be completed prior to the intervention. The intervention arm includes providing an educational intervention through the LBD process during assembly work. This intervention focuses on awareness and acquiring skills to maintain a good body posture at work and perform appropriate stretching exercises based on the most important SCT constructs. The educational content will be based on the latest national and international guidelines for the prevention of WMSDs (facts). The control group will not receive the studied intervention and will be provided them with information about ways to prevent breast cancer. The HSE expert will communicate with the participants during the intervention to teach them how to maintain a proper body posture at work and remind them to adhere to the intervention, and stretching exercises will be taught to them during breaks. Participants will receive phone calls and messages on social networks from the research team in the 12 weeks after the intervention to improve participation and adherence.

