### Recruitment

Before recruiting women, the project researchers will meet with Electronics Industries personnel (e.g., industry managers, and HSE experts) to discuss the project and its requirements. Industries that agree to provide participation opportunities to their workers who are included in the study. We expect to enroll participants consecutively during a 30-day recruitment period. All potentially eligible women will be discussed directly with the aims and potential benefits of the study.

In this study, women are not included if stretching exercises are prohibited by the occupational medicine doctor, so no harm or adverse effects are expected from participating in the trial. However, a general physician (4th authors) was invited to participate in the study. He has responsibility to consider all health aspects of the project and assess all probable medical complications during the study. Moreover, all participants are asked to report any possible side effects to be assessed by physician. The control group will receive the delayed intervention after completing the 6-month follow-up questionnaire.

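### Adverse events rest on participant self-report with no common scheduled question described, so harm reports may be incomplete and may not be comparable between the arms

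*Protocol article*

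**What the plan says.** All places are in the protocol article.

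- **Eligibility criteria:** "Participants will report potential adverse events that may occur during the trial".
- **Recruitment:** "all participants are asked to report any possible side effects to be assessed by physician". A general physician is appointed to "assess all probable medical complications during the study". The same paragraph says that "women are not included if stretching exercises are prohibited by the occupational medicine doctor, so no harm or adverse effects are expected".
- **Intervention:** "The HSE expert will communicate with the participants during the intervention to teach them how to maintain a proper body posture at work". The expert also gives reminders and teaches exercises during breaks. The programme contains both stretching and strengthening of the upper limb. Controls are given breast-cancer prevention information. In addition, "Participants will receive phone calls and messages on social networks from the research team in the 12 weeks after the intervention"; no arm is named.
- **Sampling and Blinding:** allocation is by industrial unit, and the two arms sit in two separate industries.
- **Instruments:** "The questionnaires will be completed by the two groups before the intervention, 3, 12, and 24 weeks after the educational intervention". The Nordic questionnaire is one of these instruments, and Table 3 describes it as scored yes or no.
- **Outcomes and Data analysis:** no harm outcome and no comparison of harms between arms is listed.

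**The concern.** The stated method leaves it to the worker to come forward. Three features of the design could make her readiness to do so differ by arm.

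1. Contact with trial staff about the upper limb is described for the intervention arm only.
2. The request is worded as side effects. A woman taught neck, hand and wrist exercises can readily link a sore wrist to the programme. A woman given breast-cancer information has little reason to call the same complaint a side effect.
3. Each arm is a separate industry, so any local difference in how complaints are raised coincides with the arm.

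The Recruitment section also derives an expectation of no harm from excluding women barred from stretching. That exclusion says nothing about the strengthening exercises.

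At stake is any later statement that the programme caused no adverse effects. It could rest on uneven or absent reporting, and an event that is never reported cannot be assessed. This matters because controls are to receive the programme after the 6-month follow-up, and the article foresees wider delivery by HSE experts.

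**Working it through.** The article gives no adverse-event rate, reporting probability or contact count, so there is no figure to reproduce. The check compares the passages and then illustrates how sensitive the counts are.

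**Passages side by side**

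| Question | Intervention arm | Control arm |
|---|---|---|
| Asked to report side effects? | Yes | Yes |
| Physician available to assess? | Yes | Yes |
| Upper-limb coaching by HSE expert described? | Yes | No |
| Calls and messages for 12 weeks? | Arm not stated | Arm not stated |
| Nordic questionnaire at baseline, 3, 12, 24 weeks? | Yes | Yes |
| Scheduled general adverse-event question described? | No | No |

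The request and the physician are common to both arms. The described occasions to mention a complaint are not.

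**What the Nordic questionnaire covers.** A new symptom can show as a change from no to yes, in both arms on the same schedule. A worsening of existing pain stays yes to yes. The Eligibility section cites a study in which more than 60% of comparable women reported shoulder, wrist or back pain. Assume that 60% applies to a given site here. Then 0.60 × 40 = 24 of 40 women per arm already answer yes, and worsening among them would not register on such an item. Events other than musculoskeletal ones are not covered.

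**Sensitivity of the counts (assumed values).** Let the true risk p be equal in both arms, and let r be the probability that an event is reported.

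Expected reports per arm = 40 × p × r. Apparent risk ratio = r(intervention) / r(control), whatever p is.

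With p = 10% and r(intervention) = 90%:

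| r(control) | Expected reports, intervention vs control | Apparent ratio |
|---|---|---|
| 90% | 3.6 vs 3.6 | 1.00 |
| 70% | 3.6 vs 2.8 | 1.29 |
| 50% | 3.6 vs 2.0 | 1.80 |
| 30% | 3.6 vs 1.2 | 3.00 |

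For the last row, p = 5% gives 1.8 vs 0.6 and p = 20% gives 7.2 vs 2.4. If the reporting pattern were reversed, the ratio would fall below 1 and a true excess could be hidden.

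**What silence would show.** With zero events among n women, the one-sided 95% upper bound is 1 − 0.05^(1/n).

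- n = 40: 7.2%.
- n = 40 × 0.90 = 36, after the planned 10% dropout: 8.0%.

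These bounds assume complete capture and independent women. If only half of events were reported (assumed), zero reports among 40 would bound the true risk at 0.072 / 0.5 = 14.4%. The 7.2% reflects the arm size and is not itself a defect of collection.

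**The case against.** The case on the other side is substantial.

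- **Reporting is requested.** A reader might infer that events are captured only if a worker happens to volunteer them. The Recruitment section does not support that: every participant in both arms is asked to report, and a physician is responsible for complications.
- **The likeliest harm is already asked about.** New musculoskeletal symptoms are solicited by the Nordic questionnaire in both arms at the same times. This stands and narrows the point. What remains is worsening, other events, and the absence of any stated link from those answers to the physician.
- **Contact is not quantified.** A reader might infer that the intervention arm has far more staff contact. No counts are given, the control session's length and mode are not described, and the calls are not assigned to an arm. Heavier contact is plausible but not documented.
- **No harm comparison is planned.** So no planned analysis is biased. The problem arises only if harms are later tabulated or summarised by arm.
- **This is a condensed article.** Form, wording and timing may be set out in the full protocol, and the schedule in Table 1 is not visible. The absence of such detail is therefore not held against it. The point concerns the route the article does state, and a better one is available at almost no cost.
- **The no-harm sentence is followed by safeguards.** That is true, and it softens the sentence. The inference still does not follow, because the exclusion concerns stretching and the programme also includes strengthening.

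**Conclusion.** The point holds as a minor one. Under the route the article states, harm reports may be incomplete and may not be comparable between the arms. The document does not support saying that they will be, because both arms receive the same request, the same physician cover and the same Nordic schedule.

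The size of any reporting bias cannot be derived. The range of 1.0 to 3.0 for a spurious risk ratio follows entirely from assumed reporting probabilities and shows sensitivity only. The conclusion rests on two assumptions: that coaching and the side-effect wording affect what women choose to report, and that no fuller document already sets a common query.

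**What to change.** 1. Add one identical question to the existing 3-, 12- and 24-week questionnaires in both arms: any new or worse pain, injury or other health problem since the last assessment, whatever its presumed cause. Asking without reference to cause avoids the uneven meaning of side effect in the two arms.
2. Forward every positive answer to the physician already appointed in the Recruitment section.
3. Report the solicited events descriptively by arm, and list spontaneous reports separately.
4. Reword the Recruitment sentence so that absence of harm is not inferred from the stretching exclusion alone.

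Cost: one questionnaire item and one descriptive table, with no new visits. The downside is more minor complaints to record and triage. The same question gives both arms the same prompt. It does not remove differences between the two industries, so the table should remain descriptive.
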